### Assess the diagnostic performance of Kato-Katz thick smear, Mini-FLOTAC, FECPAK^G2^ and qPCR

For each diagnostic method, the sensitivity will be calculated using the combined results of the four methods (duplicate Kato-Katz thick smear, Mini-FLOTAC, FECPAK^G2^ and qPCR) as the diagnostic ‘gold’ standard. This means that a sample is considered positive if it tested positive on at least one of the four methods. The species specificity of all methods will be set at 100%, as indicated by the morphology of the eggs or by the species-specific primer sets used in qPCR. The corresponding 95% CI for sensitivity will be calculated separately for each diagnostic method. Differences in sensitivity between methods will be assessed by a permutation test (10,000 iterations). Tukey’s method will be applied for pair-wise comparisons between the methods. The impact of infection intensity on the sensitivity within each method will be explored by a logistic regression model, which will be fitted for each of the methods with their test result (positive/negative) as the outcome and the natural log transformed mean FEC across the three methods as covariate. The predictive power of the final models will be evaluated by the proportion of the observed outcome that was correctly predicted by the model. To this end, an individual probability >0.5 will be set as a positive test result, and negative if different. Finally, the sensitivity for each of the pre-defined values of FEC will be calculated based on these models.

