### General design of the field trials

A series of drug efficacy trials will be performed in four STH endemic countries (Brazil, Ethiopia, Lao PDR and Tanzania). These trials will be designed to assess the efficacy of a single oral dose of 400 mg ALB against STH infections in SAC by a variety of stool-based diagnostic methods. At the start of each trial, schools will be visited by the local principal investigator (PI) and a team of field officers, who will explain the planned trial and sampling method to the parents and teachers and the children. At baseline, SAC will be asked to provide a fresh stool sample. All children that meet all inclusion criteria and none of the exclusion criteria (see Table 1) will be enrolled in the study. They will be treated with a single oral dose of 400 mg ALB under supervision. The ALB to be used in the different studies is manufactured by GlaxoSmithKline and donated to WHO and originates from the same production batch (Batch Nr: 335726). All collected stool samples will be processed to determine the fecal egg counts (FECs; expressed in eggs per gram of stool (EPG)) for each STH using Kato-Katz thick smear (single and duplicate), Mini-FLOTAC and FECPAK^G2^. During baseline evaluation, only stool samples found to contain at least 13 eggs on duplicate Kato-Katz or at least 15 eggs on Mini-FLOTAC for at least one of the three STHs will be preserved for further molecular analysis. Fourteen to 21 days after drug administration, a second stool sample will be collected from all the children that were excreting eggs of any STH at baseline based on Kato-Katz thick smear and Mini-FLOTAC. Stool samples will be examined by Kato-Katz thick smear (single and duplicate), Mini-FLOTAC and FECPAK^G2^. All follow-up samples will be preserved for further molecular analysis. To gain insights into the operational costs for assessing drug efficacy, the time to process stool with Kato-Katz thick smear, Mini-FLOTAC and FECPAK^G2^, and the time needed to enter data and to draft reports will be assessed. The different steps of the trials are schematized in Fig 1.

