### DNA-based methods

#### Stool preservation and DNA extraction

After performing the egg counting methods, stool samples will be preserved. At baseline, only those samples in which a sufficient number of eggs are counted for at least one STH species will be preserved (duplicate Kato-Katz thick smear: 13 eggs; Mini-FLOTAC: 15 eggs). At follow-up, all samples will be preserved, and this regardless of the number of STH eggs found. For each sample, 2 subsamples of 0.5 g will be preserved in 1 ml of absolute ethanol. A detailed SOP on sample preservation is provided in the supplementary information (S7 Info). Preserved samples will be stored in sample boxes at room temperature and shipped to Belgium for DNA extraction and subsequent molecular analysis. The DNA extraction protocol will be run on the automated QiaSymphony using a preceding mechanical lysis step by means of bead beating. This DNA protocol maximizes STH DNA yield from stool (Ayana et al, in preparation). DNA extraction will be performed at Ghent University (Belgium) and Elizabeth Tweesteden Hospital (The Netherlands). S8 Info provides a detailed SOP on DNA extraction.

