#### qPCR

All DNA extracts will be analyzed for the presence of *A*. *lumbricoides*, *T*. *trichiura*, *N*. *americanus* and *A*. *duodenale* DNA using qPCR assays previously described [37, 63, 64]. S9 Info provides a detailed SOP on how we will perform the qPCR. The output of the qPCR analysis will be expressed in genome equivalents (GE) per ml DNA extract.

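### Baseline sensitivity is judged against a four-method composite, but baseline qPCR exists only for samples that passed an egg-count threshold, so the baseline estimates are only partially verified

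*Protocol article*

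**What the plan says.** - **Reference standard.** The section on diagnostic performance combines duplicate Kato-Katz, Mini-FLOTAC, FECPAK G2 and qPCR: "a sample is considered positive if it tested positive on at least one of the four methods". It adds: "The species specificity of all methods will be set at 100" per cent. It names no time point and gives no rule for samples without qPCR.
- **Baseline preservation.** Under General design of the field trials, molecular work is limited to "only stool samples found to contain at least 13 eggs on duplicate Kato-Katz or at least 15 eggs on Mini-FLOTAC". Reaching the count for any single species is enough. Stool preservation and DNA extraction repeats the rule: "At baseline, only those samples in which a sufficient number of eggs are counted for at least one STH species will be preserved".
- **qPCR.** It is run on extracts, so on preserved stool only: "All DNA extracts will be analyzed for the presence of" each of the four species.
- **Follow-up.** There is no egg threshold: "At follow-up, all samples will be preserved, and this regardless of the number of STH eggs found". The children sampled are a selected group, however: "a second stool sample will be collected from all the children that were excreting eggs of any STH at baseline", as judged by Kato-Katz and Mini-FLOTAC.
- **Purpose of qPCR.** The Discussion says that including qPCR should make the sensitivity estimates more accurate, because no gold standard exists.

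**The concern.** qPCR belongs in the composite because it can reveal infections that all three egg counts miss. At baseline, that component is obtained only where one of two methods under evaluation has already given a fairly high count. This is partial verification: whether the reference is fully ascertained depends on the results of the tests being judged.

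Diagnostic performance is a stated objective and feeds the choice of recommended method. The planned permutation tests and Tukey comparisons of sensitivity would carry any distortion with them. The analysis cannot repair it later, because stool that was not preserved has no qPCR result.

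**Working it through.** **1. Figures in the plan.** The plan gives no sensitivity, power or sample size for this objective, so there is none to reproduce. The 110, 100 and 12 complete cases concern ERR equivalence. The Kato-Katz factor checks: 1 / (2 × 0.0417 g) = 11.99, or 12. The threshold is therefore 13 × 12 = 156 EPG, inside the low-intensity class of all three species (upper limits 4,999, 999 and 1,999 EPG).

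**2. What the rules imply, without simulation.** A baseline sample that passes the threshold for a species is already egg-positive for that species, so its qPCR result cannot change the composite. qPCR can add a baseline positive for a species only when the sample was preserved because of another species. At follow-up, qPCR is available whatever the egg count.

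**3. How hard the threshold filters.** The check uses Poisson counts with 0.0834 g read on duplicate Kato-Katz and an assumed 0.1 g on Mini-FLOTAC.

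| True EPG | P(Kato-Katz ≥1 egg) | P(passes 13/15 rule) |
|---|---|---|
| 24 | 0.865 | 0.000 |
| 50 | 0.985 | 0.001 |
| 100 | 1.000 | 0.158 |
| 156 | 1.000 | 0.813 |
| 300 | 1.000 | 1.000 |

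**4. Size, by simulation.** There were 1,000,000 infected samples in each of 16 scenarios. The following inputs are assumptions, not taken from the document, except where marked:
- EPG is gamma-distributed, with mean 100 to 1,000 and shape 0.3 or 0.6.
- Within-stool variation is gamma with shape 1.5.
- FECPAK G2 reads 3 g × 0.91 ml / 95 ml = 0.029 g (volumes from the FECPAK G2 section), with 50% egg recovery assumed.
- qPCR detection is 1 − exp(−EPG/20) or 1 − exp(−EPG/100).
- Either 0% or 30% of samples are preserved regardless of this species' count, to represent co-infection.

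Across scenarios, 34–78% of composite positives would have a qPCR result. One scenario (mean 300 EPG, shape 0.3, qPCR scale 20 EPG, no co-infection) gives these sensitivities:

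| Analysis set | Kato-Katz | Mini-FLOTAC | FECPAK G2 | qPCR |
|---|---|---|---|---|
| qPCR on every sample | 86.6% | 88.5% | 62.9% | 86.3% |
| Preserved samples only | 98.9% | 99.1% | 87.1% | 99.7% |
| All samples, absent qPCR = negative | 88.7% | 90.6% | 64.4% | 53.1% |

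Here qPCR ranks third, first or last depending only on the analysis set.

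Change in points from the row with qPCR on every sample, over all scenarios:

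| Analysis set | Kato-Katz | Mini-FLOTAC | FECPAK G2 | qPCR |
|---|---|---|---|---|
| Preserved only | +4 to +18 | +4 to +15 | +10 to +31 | +5 to +34 |
| Absent qPCR = negative | at most +3 | at most +3 | at most +3 | −8 to −45 |

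The low ends for preserved samples come from the scenarios with 30% co-infection. Example at mean 100 EPG, shape 0.3 and qPCR scale 20 EPG: the Kato-Katz inflation is 98.2 − 80.4 = 17.8 points without co-infection and 88.3 − 80.4 = 7.9 with it.

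**The case against.** The strongest reply is that the section never says sensitivity is computed at baseline, on complete cases, or with absent qPCR scored negative. An article may leave the analysis set to a fuller document. On follow-up samples the problem does not arise. This stands as a reason not to claim that a particular bias will occur. It does not dispose of the point: the article itself fixes both the preservation rule and the reference standard, and at baseline each obvious way of combining them is biased.

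Four further points deserve weight.

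- **Light samples are not wholly excluded.** A reader might infer that qPCR never meets light or egg-negative samples. The document does not support that. The threshold applies to at least one species, every extract is tested for all species, and all follow-up samples are kept. Co-infection shrinks the bias without removing it.
- **Direction.** A reader might infer that the rule favours Kato-Katz and Mini-FLOTAC because they decide which samples enter. Entry does nearly guarantee their positivity, but on preserved samples FECPAK G2 gains more than either. In the example, the gap between Kato-Katz and FECPAK G2 narrows from 86.6 − 62.9 = 23.7 points to 98.9 − 87.1 = 11.8.
- **Partial mitigation.** The planned logistic models report sensitivity by egg count. They address the shift in intensity among egg-positive samples but cannot recover qPCR-only positives that were never tested.
- **Scope.** The sample size and the stated use-case concern ERR. The comparison of ERR between egg-count methods does not use qPCR and is untouched.

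**Conclusion.** The point holds for baseline samples. A reference that includes qPCR is applied without restriction, although qPCR is obtained at baseline only above a threshold on two of the methods under test. That structure follows from the stated rules alone.

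The sizes are illustrative. They depend on assumed intensity distributions, egg recoveries, qPCR detection curves and degree of co-infection, none of which the document gives. The direction is upward for all four methods if only preserved samples are analysed. For qPCR it reverses if absent results count as negative. It would be tempting to conclude that the method ranking or the trial's main comparison is invalid. The document does not support that, because the analysis set is unstated and the ERR comparison is unaffected. Severity: should-fix.

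**What to change.** State the analysis set by time point in the section on diagnostic performance:

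1. **Follow-up:** compute the four-method composite sensitivities and their pair-wise tests here, because "All follow-up samples will be preserved for further molecular analysis".
2. **Baseline:** compare duplicate Kato-Katz, Mini-FLOTAC and FECPAK G2 against a three-method egg-count composite on all samples.
3. **Baseline qPCR:** report sensitivity only as conditional on preserved samples, and keep it out of the ranking.

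This changes analysis wording and needs no laboratory work. Two costs should be stated. First, follow-up samples are fewer and lighter, and come only from treated children who were egg-positive at baseline on Kato-Katz and Mini-FLOTAC. The four-method estimates apply to that population. Second, the three-method composite still misses infections that all three egg counts miss. Without co-infection, its values equal the egg-count figures in the row where absent qPCR counts as negative, so in these scenarios they exceed the full four-method values by at most about 3 points.

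If sampling is still open, qPCR on a random subsample of below-threshold baseline stool, weighted by the inverse of the testing probability, would allow a four-method baseline comparison. That option does require extra preservation and laboratory work.

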### Intensity of infection

For egg counting methods, the agreement in egg counts will be evaluated by permutation tests (10,000 iterations) based on (i) Pearson’s correlation coefficient and (ii) the differences in FECs. Tukey’s method will be applied for pair-wise comparisons within each STH species. For qPCR, the agreement in GE numbers and FECs obtained by duplicate Kato-Katz thick smear will be evaluated by permutation tests (10,000 iterations) based on Pearson’s correlation coefficient.

Samples containing helminth eggs will be classified into low, moderate, and heavy infection intensity according to FECs obtained by duplicate Kato-Katz and following the thresholds proposed by WHO; for *A*. *lumbricoides* these are 1–4,999 EPG, 5,000–49,999 EPG, and >49,999 EPG; for *T*. *trichiura* these are 1–999 EPG, 1000–9,999 EPG, and >9,999 EPG; and for hookworm these are 1–1,999 EPG, 2,000–3,999 EPG and >3,999 EPG (WHO, 1998). For each of the other diagnostic methods, a receiver operating characteristic analysis will be performed to determine the corresponding FECs / GE numbers that allow classification of the infections into low, moderate and heavy using duplicate Kato-Katz thick smear as a reference. Finally, the proportion samples correctly classified as having a low, moderately and heavy infection intensity will be assessed separately for single Kato-Katz thick smear, Mini-FLOTAC, FECPAK^G2^ and qPCR.

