### Sample size calculation

A sample size was calculated to test the alternative hypothesis that FECPAK^G2^, Mini-FLOTAC and single Kato-Katz thick smear provide equivalent drug efficacy results measured by ERRs compared to a duplicate Kato-Katz thick smear. Given the differences in drug efficacy of ALB across the STH species [15, 21] (*Ascaris*: ~99%, hookworms: ~96%, *Trichuris*: ~65%), a level of equivalence that is acceptable for *Trichuris* may not be acceptable for *Ascaris*. Therefore, a species-specific level of equivalence was used. For *Ascaris* the level of equivalence was set at 2.5-point percentage, for hookworms and *Trichuris* the level of equivalence was set at 5.0 and 10 point percentage, respectively. Both type I and II errors were set at 0.05.

To calculate the corresponding sample size for each of the STH species, we performed a simulation study. This simulation study considered (i) variation in ERR and baseline FECs across and within STH species, (ii) variation in FECs introduced by the egg counting process, (iii) the paired ERR results across egg count methods, and (iv) a post-hoc correction for a pair-wise comparison. Based on the simulation, at least 110, 100 and 12 complete cases are required for *Trichuris*, hookworm and *Ascaris*, respectively. A detailed description of the sample size calculation is available in the supplementary information (S1 Info).

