### Egg counting methods

#### Kato-Katz thick smear

Kato-Katz thick smears will be prepared on microscope slides using a square template with a hole of 6 mm diameter and 1.5 mm deep, which is assumed to sample 41.7 mg of stool [61]. Two Kato-Katz thick smears will be prepared per sample (slide A and B) and to avoid clearing of hookworm eggs, all slides will be examined within 30–60 min for the presence of STH eggs. The number *A*. *lumbricoides*, *T*. *trichiura* and hookworm eggs will be counted and recorded per slide. Slide A will represent a single Kato-Katz thick smear. For the duplicate Kato-Katz thick smear, the egg counts of slide A and B are added and multiplied by 12 to obtain the FEC. A detailed SOP on how the duplicate Kato-Katz thick smears will be processed is provided in S3 Info.

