### Statistical data analysis

After data collection and quality control, all data will be combined in a final, protected dataset for statistical analysis. After finishing work package 1, this dataset will be made available on the Starworms website (www.starworms.org). All statistical analysis will be performed in R (R Development Core Team, 2016).

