### Assessment of the impact of previously conducted PC in reducing STH morbidity

We will evaluate both the prevalence and intensity of each different STH species in each of the four different study sites. The percentage of individuals included in the different classes of infection intensity will be reported in order to assess the efficacy of the PC intervention conducted until then in eliminating STH infection of moderate and heavy intensity.

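### Intensity-class cut-offs are fitted by ROC analysis and, on the plain reading, scored in the same samples with no optimism correction, so the reported proportions correctly classified are biased upward

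*Protocol article*

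**What the plan says.** Under the heading Intensity of infection, the protocol article sets out three steps.

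1. Egg-positive samples are placed in the low, moderate or heavy class "according to FECs obtained by duplicate Kato-Katz and following the thresholds proposed by WHO". The reference limits are therefore fixed in advance.
2. For every other method, "a receiver operating characteristic analysis will be performed to determine the corresponding FECs / GE numbers that allow classification of the infections". These cut-offs are estimated from the trial data. The criterion for picking a point on the curve is not named.
3. "Finally, the proportion samples correctly classified as having a low, moderately and heavy infection intensity will be assessed separately for single Kato-Katz thick smear", and likewise for Mini-FLOTAC, FECPAK-G2 and qPCR.

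Under Statistical data analysis, "all data will be combined in a final, protected dataset for statistical analysis". No validation set, split, cross-validation or bootstrap correction is described for this analysis.

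Two other sections bear on the size of the problem. The sample size is set for equivalence of egg reduction rates: "at least 110, 100 and 12 complete cases are required for" Trichuris, hookworm and Ascaris respectively. On how many children fall in each class, the article says only that "The percentage of individuals included in the different classes of infection intensity will be reported".

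**The concern.** A cut-off chosen because it separates the classes well in one set of samples will look better in that set than in new samples. If the proportion correctly classified is computed in the samples that produced the cut-off, it overstates what the method would achieve elsewhere. The bias for a given class depends mainly on how many samples that class holds, so a large total does not protect a small class.

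At stake is how well each method appears to reproduce the intensity classes. The study's overall aim is to recommend diagnostic methods, and a reader would take these proportions as the accuracy to expect in fresh samples. A class with very few samples could show near-perfect accuracy that is largely an artefact of fitting.

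**Working it through.** **No figure to reproduce.** The article gives no expected accuracy, class frequency or sample size for the ROC analysis, so the check is a simulation under stated assumptions.

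**Inputs from the article**
- Three classes, hence two cut-offs per method and species; fixed reference limits; one combined dataset.
- Minimum complete cases: 110, 100 and 12. These were derived for another purpose and serve here only as a lower scale.
- The Pyrosequencing section plans 60 positive baseline samples per species at each of four sites: 60 × 4 = 240. This is a more realistic lower scale for the number of positives.

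**Assumptions, not in the article**
- Log intensities by reference and index method are bivariate normal, with correlation 0.6, 0.8 or 0.95.
- Class mix is 2% heavy with 20% moderate, 5% with 20%, or 15% with 30%.
- Each cut-off (low versus higher; heavy versus lower) maximises the Youden index.

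**Formula.** Optimism = (proportion correct in the n samples that set the cut-offs) − (proportion correct with the same cut-offs in 100,000 new samples). There were 1,500 runs per setting and 5 sample sizes × 3 correlations × 3 class mixes = 45 settings. Runs with an empty class were skipped, because no cut-off can be set.

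**Worked examples at correlation 0.8**
- n = 110, 5% heavy (110 × 0.05 = 5.5 expected). All classes: 0.744 − 0.703 = 0.041, or 4.1 points. Heavy class: 0.962 − 0.791 = 0.171, or 17.1 points.
- n = 400, 2% heavy (8 expected). All classes: 0.735 − 0.718 = 0.017, or 1.7 points. Heavy class: 0.973 − 0.836 = 0.137, or 13.7 points.
- n = 1000, 5% heavy (50 expected). All classes: 0.702 − 0.692 = 0.010, or 1.0 point. Heavy class: 0.916 − 0.872 = 0.044, or 4.4 points.

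**Ranges over the three correlations (percentage points)**

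| n | Expected heavy samples | All-class optimism | Heavy-class optimism |
|---|---|---|---|
| 100–110 | about 2 | 3.0–4.1 | 24.4–33.7 |
| 100–110 | about 5 | 3.6–4.7 | 15.6–20.1 |
| 100–110 | about 15 | 4.4–5.6 | 6.6–9.0 |
| 400 | 8 | 1.5–1.8 | 10.7–15.0 |
| 400 | 20 | 1.5–2.0 | 5.6–8.9 |
| 400 | 60 | 2.1–2.6 | 2.9–4.3 |
| 1000 | 20 | 0.9–1.1 | 4.7–8.2 |
| 1000 | 50 | 0.9–1.2 | 3.0–5.1 |
| 1000 | 150 | 1.2–1.4 | 1.7–2.1 |

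Optimism was positive in all 45 settings. The two rows with 20 heavy samples give similar heavy-class bias although n differs by a factor of 2.5, so for that class the class count matters more than the total. A separate run at correlation 0.8 put all-class optimism at about 2 to 3 points for n between 240 and 400.

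**The extreme of 12 samples.** With heavy share h and moderate share m, the chance that at least one of these two classes is empty is (1 − h)^12 + (1 − m)^12 − (1 − h − m)^12.
- h = 0.02, m = 0.20: 0.785 + 0.069 − 0.051 = 0.803.
- h = 0.05, m = 0.20: 0.540 + 0.069 − 0.032 = 0.577.

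So in about 58% to 80% of such datasets no full set of cut-offs could be fitted. Over the class mixes, in the runs that could be fitted, all-class optimism was 10 to 18 points and heavy-class optimism 20 to 37.

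**The case against.** The strongest objection is that reuse of the same samples is inferred from silence. The article gives this analysis a few sentences, and internal validation could sit in a full protocol or analysis plan that is not shown. That stands as a caution. However, the article does fix a sequence (fit, then score) within one combined dataset, and carrying it out as written gives a biased figure. The point is about the procedure described, not about missing detail.

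Several stronger readings are tempting and do not hold.

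- A reader might infer that heavy infections are rare here, so the heavy-class figure must be badly inflated. The article never gives the frequency. Its Study population section notes that school-aged children usually carry the highest worm burdens for Ascaris and Trichuris. The large figures apply only if heavy samples turn out to be few.
- A reader might take 110, 100 or 12 as the ROC sample sizes. They are minimum complete-case numbers for the equivalence test. All egg-positive samples enter the classification, and the pyrosequencing plan alone anticipates 240 positives per species. At that scale the all-class bias is small.
- A reader might infer more inflation for methods with coarser counts. Nothing in the article or in this check compares methods in that way.
- A reader might infer that the fitted cut-offs will be handed to other programmes. The Study objectives send the recommended methods to work package 2 and do not mention these cut-offs.

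It is also fair that this is a secondary, descriptive analysis.

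**Conclusion.** The concern holds in limited form. As described, the proportions correctly classified will be biased upward. The direction is firm for any cut-off tuned to the data. The size rests on the assumed intensity distribution, correlations, class mixes and Youden criterion.

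- All classes together: about 3 to 6 points at 100 to 110 samples and about 1.5 to 3 at 240 to 400.
- Heavy class: about 11 to 34 points if only 2 to 8 samples are heavy, and about 2 to 5 points with 50 or more.

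Which heavy-class figure applies cannot be told from the document. The egg reduction rate equivalence comparison, for which the trial was sized, is not affected. The point is a cheap improvement, not an error that threatens the study's main conclusions.

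**What to change.** - Keep the cut-offs estimated from all data as the recommended values, and name the ROC criterion used to pick them.
- Report the proportion correctly classified, overall and per class, with bootstrap optimism correction or with cross-validation stratified by class. Where baseline and follow-up samples from one child both enter, resample by child.
- Give the number of samples in each class and a confidence interval beside each proportion.
- Do not estimate a cut-off where a class has too few samples for the resampling to work, and state that minimum before the analysis.
- Use leave-one-site-out only as an added check of transportability, and only where each site has enough cases in each class. It mixes between-site differences with optimism and breaks down when the heavy samples sit at one or two sites.

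One related caution: "Slide A will represent a single Kato-Katz thick smear", and slide A is also half of the duplicate reference. Its agreement is raised by that overlap, which resampling will not remove, so a sentence should say so when it is compared with the other methods.

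The cost is a little more R code and slightly lower reported accuracy. No new data and no change in design are needed.
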